### Randomization and blinding

2.4

Randomization will be performed at the class level. After baseline assessments are completed, participating classes will be randomly assigned in a 1:1 ratio to either the intervention group (motor-focused physical education) or the control group (ordinary physical education). The allocation sequence will be generated by an independent researcher using a computer-based random number generator and will not be disclosed to the assessment team until all baseline testing has concluded.

Due to the nature of the intervention, it is not possible to blind teachers or participants to group allocation. However, outcome assessors will remain blinded throughout the study. Specifically, individuals conducting the motor skill assessments and EEG recordings will not be informed of class assignments. To further reduce bias, video recordings of motor skill performances will be scored by two independent raters who are blinded to intervention status and assessment time point. Data analysts will also be blinded to group labels until the primary analyses are completed.

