### Study design

2.1

This study is a prospective, two-arm, parallel-group, cluster-randomized controlled trial designed to evaluate the effects of a semester-long (approximately 16 weeks) motor-focused physical education program on gross motor competence and neurodevelopment in preschool children. The study will be conducted in kindergartens from Changsha, Hunan Province, China. The trial follows the recommendations of the SPIRIT 2025 statement for standardized protocol reporting (11). As shown in Figure 1, all participants will undergo eligibility screening, informed consent, and baseline assessments prior to randomization (week 0). The intervention phase spans 16 weeks, during which classes receive either structured motor-focused physical education or ordinary physical education. Outcome assessments are scheduled at baseline (week 0) and immediately post-intervention (week 16). This schedule ensures standardized evaluation and facilitates examination of both motor and neural effects of the intervention.

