### Participants

2.2

Children eligible for this study will be those enrolled in participating kindergartens and aged between 4 and 6 years at the time of recruitment. Participants must be physically healthy and able to engage safely in structured physical education activities. Only children whose parents or legal guardians provide written informed consent will be included.

Children will be excluded if they (1) have diagnosed neurological, developmental, or musculoskeletal disorders that may interfere with motor performance or EEG measurement; (2) are currently enrolled in specialized sports or motor-training programs outside the kindergarten curriculum; or (3) are unable to comply with EEG assessment procedures due to behavioral or sensory intolerance. Children with mild, well-managed conditions (e.g., attention deficit) will not be excluded.

Recruitment will be carried out in collaboration with kindergarten administrators and teachers. Parents will receive written and verbal information about the study objectives, procedures, and potential benefits and risks. Recruitment meetings will be held in participating school to address questions from parents and staff. Consent forms will be distributed to parents, and only children with returned signed consent will be enrolled.

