### Sample size

2.3

The sample size was calculated to detect meaningful differences in gross motor competence between the intervention and control groups, while accounting for the cluster-randomized design. Previous intervention trials and meta-analyses of preschool motor-skill programs have consistently reported large effect sizes, often exceeding 1.0, for improvements in fundamental motor skills (7). Based on this evidence, we adopted an assumption of an effect size of 1.0 for between-group differences.

Using a two-tailed alpha of 0.05 and a statistical power of 80%, an individually randomized design would require approximately 21 children per group. Because this study uses class-level randomization, the required sample size was adjusted for clustering. Assuming an average class size of 25 and an intra-class correlation coefficient of 0.05, the design effect is estimated at 2.2. This adjustment results in an effective sample size of 46 children per group, or 92 children in total. To accommodate an anticipated dropout rate of 15%, we plan to recruit approximately 110 children overall, distributed across four to six kindergarten classes in Changsha city.

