The frequency and duration of control sessions will match those of the intervention group (three sessions per week, 30–40 min per session) to ensure comparable exposure time. Teachers assigned to control classes will not receive motor-focused training workshops, structured lesson manuals, or feedback related to the intervention program. Classes within participating kindergartens are administratively distinct, and teaching staff do not rotate between intervention and control classes during the study period. Intervention materials will be provided exclusively to teachers in the intervention arm, and research staff responsible for fidelity monitoring will not provide instructional guidance to control teachers. These procedures are intended to minimize contamination while preserving the ecological validity of the school-based design.

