### Statistical analysis

2.8

All analyses will follow the intention-to-treat principle, with all children analyzed according to their randomized class regardless of adherence or attendance. Descriptive statistics will be reported for baseline demographic and developmental characteristics, including age, sex, height, weight, and baseline TGMD-3 scores, to assess comparability between groups. Continuous variables will be summarized using means and standard deviations, while categorical variables will be summarized using frequencies and percentages.

For the primary outcome of gross motor competence, linear mixed-effects models will be used to examine group (intervention vs. control) by time (baseline vs. post-intervention) interactions, accounting for clustering at the class level. Models will include random intercepts for class and child, and fixed effects for group, time, and the group-by-time interaction. Relevant covariates, including age and sex, will be included where appropriate. Because the number of clusters (classes) in the present study is relatively small, degrees of freedom for fixed effects will be estimated using the Satterthwaite approximation within the linear mixed-effects modeling framework. This approach reduces potential underestimation of standard errors and helps control Type-I error rates in studies with limited cluster numbers.

For EEG outcomes, analyses will follow the pre-specified hierarchy of neural endpoints. The primary EEG analysis will focus on frontal theta power during resting state. A secondary task-related neural index will be the N2 amplitude elicited during the Go/No-Go task. Separate linear mixed-effects models will be constructed for each neural endpoint to evaluate group-by-time interactions, using the same clustering structure as described for the primary motor outcome (random intercepts for class and child).

Additional EEG measures will include spectral power indices in the alpha and beta frequency bands, which will be analyzed using similar mixed-effects models. To account for multiple comparisons across these secondary neural measures, false discovery rate adjustments will be applied. These analyses will be interpreted as supportive and contextual rather than confirmatory.

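### No restriction of the class randomisation by kindergarten or age level is described, so with four to six classes arm can coincide with kindergarten; how likely depends on a layout the protocol does not give

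*Protocol article*

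**What the plan says.** Section 2.3 plans about 110 children, "distributed across four to six kindergarten classes in Changsha city". Section 2.1 speaks of kindergartens in the plural: "The study will be conducted in kindergartens from Changsha, Hunan Province, China". Neither the number of kindergartens nor the number of classes in each is given.

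On allocation, section 2.4 states that "Randomization will be performed at the class level" and that, once baseline testing is finished, "participating classes will be randomly assigned in a 1:1 ratio to either the intervention group (motor-focused physical education) or the control group". On the sequence it says: "The allocation sequence will be generated by an independent researcher using a computer-based random number generator". Concealment from the assessors until baseline is complete is also described. Stratification, matching or any other constraint is not mentioned.

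Section 2.5, on contamination, says: "Classes within participating kindergartens are administratively distinct, and teaching staff do not rotate between intervention and control classes during the study period". Section 2.2 admits children "aged between 4 and 6 years at the time of recruitment" and does not say whether classes are graded by age.

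The primary model in section 2.8 has random intercepts for class and child, and fixed effects for group, time and their interaction. There is no kindergarten term. On other terms it says: "Relevant covariates, including age and sex, will be included where appropriate". The section recognises that clusters are few and responds with Satterthwaite degrees of freedom.

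**The concern.** With four to six units, randomisation cannot be relied on to balance anything. Kindergartens may differ in space, equipment and everyday programme, and older and younger classes may gain motor skill at different rates over a semester. If every class of one kindergarten falls in one arm and every class of the other kindergarten in the other arm, site and arm are the same variable, and no later analysis can separate them. The Satterthwaite correction concerns standard errors and does nothing about this. Allocation is therefore the only point at which the problem can be prevented. Section 2.4 sets out the unit, timing, ratio, generator and concealment, but nothing that would prevent it.

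**Working it through.** The protocol states no probability of confounding, so there is no figure of its own to reproduce.

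**Inputs.** Four to six classes (section 2.3); class as the unit, 1:1 ratio, baseline before allocation (section 2.4); more than one kindergarten (section 2.1). Assumed, because not stated: classes per kindergarten, and an equal split of classes between arms (2 v 3 when there are five).

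**Step 1: full coincidence of arm and kindergarten.** The number of equal splits is C(4,2) = 6 for four classes and C(6,3) = 20 for six. For five classes it is C(5,2) = 10, with two classes in a given arm. An allocation counts as fully coincident when the two arms share no kindergarten. The last column counts the allocations in which every kindergarten with two or more classes supplies both arms.

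| Assumed classes per kindergarten | Possible splits | Arm fully coincides with kindergarten | Left after restriction |
|---|---|---|---|
| 2 + 2 | 6 | 2 (33%) | 2 × 2 = 4 |
| 2 + 1 + 1 | 6 | 2 (33%) | 2 × 2 = 4 |
| 1 + 3 | 6 | 0 | 6 |
| 1 + 1 + 1 + 1 | 6 | 6 (100%) | restriction cannot help |
| 2 + 3 (2 v 3 split) | 10 | 1 (10%) | 2 × 3 = 6 |
| 3 + 3 | 20 | 2 (10%) | 20 − 2 = 18 |
| 2 + 2 + 2 | 20 | 0 | 2 × 2 × 2 = 8 |

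In the 2 + 2 + 2 layout, 20 − 8 = 12 allocations (60%) leave at least one kindergarten wholly in one arm. In each of those 12, one kindergarten is split, one lies wholly in the intervention arm and one wholly in the control arm. That is imbalance, not full confounding.

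**Step 2: what reaches the estimate.** With complete data at two time points, the group-by-time estimate is the mean change in the intervention arm minus the mean change in the control arm. Write a child's change as τ + θ × arm + s(k) + error, where θ is the intervention effect and s(k) is the 16-week gain peculiar to kindergarten k. Any stable difference in level cancels in the change. With equal class sizes:

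- 2 + 2, arm coincident with kindergarten: the expected estimate is θ + s(1) − s(2).
- 2 + 2, one class of each kindergarten per arm: both arms carry [s(1) + s(2)]/2, so the expected estimate is θ.
- 2 + 2 + 2, kindergarten 1 wholly intervention, 3 wholly control, 2 split: θ + [2s(1) + s(2)]/3 − [2s(3) + s(2)]/3 = θ + 2[s(1) − s(3)]/3.

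The same algebra holds with age level in place of kindergarten. A main effect of age, sex or kindergarten is constant over time, so it cancels from the change and leaves this estimate as it was. Only a by-time term, or adjustment in a model of the post-test score, acts on gain.

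**Step 3: kindergarten and age level together.** Assume two kindergartens, each with one younger and one older class. Of the 6 splits, 2 align arm with kindergarten, 2 align arm with age level, and 6 − 2 − 2 = 2 align with neither. So 4 of 6 (67%) confound arm with one factor or the other. Restricting on kindergarten alone leaves 4 splits, of which 2 align with age level. The chance of age confounding then rises from 2/6 (33%) to 2/4 (50%).

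**Step 4: degrees of freedom.** If inference uses class-level degrees of freedom, four classes give 4 − 2 = 2, and two pairs give 2 − 1 = 1 (two-sided 5% critical t from 4.30 to 12.71). Six classes give 4, and three pairs give 2 (2.78 to 4.30).

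**The case against.** The strongest reply is that a journal article condenses the full protocol, and that a 1:1 computer-generated sequence is compatible with stratified generation. That stands in part. A reader might infer that the allocation is unrestricted, but the document never says so; it describes no restriction, and that is all that can be claimed.

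Three other stronger readings also fail:

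- One in three might be taken as the trial's risk, or as its upper limit. It is neither. Depending on layout the figure for kindergarten runs from 0% to 100%, and no layout is given.
- The 12 of 20 figure might be read as full confounding. In those allocations one kindergarten is still split, so site and arm remain separable, although with kindergarten-by-time terms the contrast would rest on that kindergarten alone.
- Section 2.5 might be read as promising both arms in every kindergarten. It contemplates intervention and control classes within kindergartens but does not guarantee them.

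It can also be said that baseline measurement removes stable differences, that control sessions match the intervention in frequency and duration, and that the protocol gives no evidence that gain differs by site or age. All of this is fair. It narrows the threat to differential gain, whose size cannot be taken from the documents. It does not remove it, and the adjustment for age in section 2.8, if entered as a main effect, would not either.

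Finally, matching very few clusters is a real trade-off because of the degrees of freedom it can cost. That argues against obligatory pair effects in the model, not against restricting the allocation.

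**Conclusion.** The point holds in conditional form. As section 2.4 is written, nothing prevents arm from coinciding with kindergarten, and if it does, the primary group-by-time effect cannot be separated from a site difference in gain. The chance is 33% for two kindergartens of two classes, 10% for two of three, none for three of two, and certain with one class per kindergarten, all under an equal split. Confounding with age level carries the same figures where age levels divide the classes in the same way, but only if classes are age-graded, which is an assumption. The size of any bias cannot be given: it equals the difference in 16-week gain between the aliased groups, for which the documents offer no figure. If restriction is already planned, one sentence in section 2.4 settles the matter. If not, it should be added before allocation, because it cannot be repaired afterwards.

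**What to change.** Before allocation, state the number of kindergartens, the classes in each and whether classes are age-graded. Then make these changes:

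1. In section 2.4, restrict the randomisation so that each kindergarten with two or more classes supplies both arms, and draw at random from the allocations that meet this. Where possible, recruit at least two classes per kindergarten, since single-class kindergartens gain nothing from the restriction.
2. Among those allocations, prefer the ones balanced on class age level and class mean baseline TGMD-3. Both will be known, because baseline precedes randomisation. If classes are age-graded, do not balance on kindergarten alone (step 3 of the working).
3. In section 2.8, if kindergarten or age is adjusted for, enter it as a by-time term or in a baseline-adjusted model of the post-test score, not only as a main effect. Do not require pair fixed effects.

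The cost is a few sentences of text and fewer possible allocations: 6 to 4 for two kindergartens of two, 20 to 8 for three of two, and only 2 in the two-by-two site-and-age layout if both factors are balanced. Adjustment also uses cluster-level degrees of freedom, for example from 2 to 1 with four classes in two pairs. That is a reason to put the protection into the allocation and keep the model lean.

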### Intervention

2.5

Children assigned to the intervention arm will receive a structured, motor-focused physical education program designed to strengthen fundamental motor skills through progressive, developmentally appropriate movement experiences. The program will be delivered three times per week for approximately 30 to 40 min per session over one academic semester (16 weeks). Each session will follow a standardized structure consisting of a warm-up phase, a structured skill-development phase, and a cool-down period.

Sessions will begin with a 5–7 min warm-up consisting of light locomotor activities, rhythm-based movements, and dynamic stretching designed to prepare children for physical activity. The main skill-development phase (approximately 20–25 min) will emphasize systematic practice of locomotor skills such as running, hopping, sliding, and jumping, as well as object-control skills including throwing, catching, striking, and kicking. Activities will be organized through small-group drills, obstacle courses, and skill stations that progressively increase in complexity across the intervention period. A short game-based integration phase (approximately 5–8 min) will allow children to apply practiced skills within simplified movement games designed to promote coordination, agility, and cooperative interaction. Finally, sessions will conclude with a 3–5 min cool-down, including light stretching and rhythm-based relaxation activities.

The intervention will be delivered by regular kindergarten teachers who will undergo structured preparatory training prior to study initiation. Teachers in the intervention arm will participate in workshop sessions led by the research team, during which they will receive detailed lesson manuals outlining session objectives, activity progressions, instructional cues, and safety procedures. Standardized written materials will be provided to promote consistency across classrooms.

To strengthen intervention fidelity, multiple monitoring procedures will be implemented. Trained research staff will conduct biweekly on-site observations using a standardized fidelity checklist assessing adherence to session structure, accurate delivery of prescribed activities, progression of task difficulty, and child engagement. Each observed session will receive a quantitative adherence score reflecting the proportion of prescribed components implemented as intended. When deviations from protocol are identified, structured feedback will be provided promptly to teachers, and additional guidance or refresher instruction will be arranged if necessary. In addition, a randomly selected subset of sessions will be video-recorded and independently reviewed by members of the research team to verify fidelity ratings and ensure inter-rater consistency. Fidelity data will be summarized and reported in trial outcomes to enhance transparency.

To monitor exercise intensity and ensure that overall physical activity exposure remains comparable between groups, heart rate (HR) will be measured in a randomly selected subsample of children using wearable heart-rate monitors (Huawei Band 10, Huawei Technologies, Shenzhen, China). In each participating class, five children will be randomly selected to wear the device during selected physical education sessions throughout the intervention period. HR will be recorded continuously during the session, providing an objective estimate of exercise intensity and allowing verification that activities reach moderate-to-vigorous physical activity levels typical of preschool physical education. Monitoring will be conducted in both intervention and control classes to ensure comparable overall cardiovascular exertion.

Children assigned to the control arm will continue to receive the standard kindergarten physical education curriculum delivered by their regular teachers. In participating schools, ordinary physical education typically consists of rhythmic exercises, unstructured free play, and simple group games designed to promote enjoyment and social interaction. These sessions do not follow a structured progression targeting specific locomotor or object-control competencies and do not include standardized motor-development lesson plans.

The frequency and duration of control sessions will match those of the intervention group (three sessions per week, 30–40 min per session) to ensure comparable exposure time. Teachers assigned to control classes will not receive motor-focused training workshops, structured lesson manuals, or feedback related to the intervention program. Classes within participating kindergartens are administratively distinct, and teaching staff do not rotate between intervention and control classes during the study period. Intervention materials will be provided exclusively to teachers in the intervention arm, and research staff responsible for fidelity monitoring will not provide instructional guidance to control teachers. These procedures are intended to minimize contamination while preserving the ecological validity of the school-based design.

### Outcomes and data collection procedures

2.6

The primary outcome of this study will be children's gross motor competence, assessed using the Test of Gross Motor Development, Third Edition (TGMD-3). This standardized instrument provides separate scores for locomotor and object-control skills, as well as a composite gross motor quotient. The TGMD-3 is widely used in early childhood research and has demonstrated strong reliability and validity in preschool populations (12). Assessments will be conducted at baseline and again following the 16-week intervention period in familiar school environments. Children will complete locomotor and object-control subtests under standardized instructions provided by trained assessors. Performances will be video-recorded and subsequently scored by blinded raters.

Secondary outcomes will include neurodevelopmental indicators measured using portable EEG recorded with the BrainLink Lite system (Macrotellect, Shenzhen, China). The device uses dry-electrode technology and records EEG activity from a single frontal electrode positioned at Fp1 according to the international 10–20 system, with reference and ground provided via an ear-clip electrode. Signals are sampled at 512 Hz and transmitted wirelessly to a recording computer via Bluetooth. Similar portable EEG systems have been used in previous research examining cognitive and affective processes in naturalistic settings (13).

Although multi-channel research-grade EEG systems provide higher spatial resolution, their use in preschool populations is often constrained by long preparation times, the need for conductive gels, and reduced tolerance among young children in school environments. Portable single-channel systems therefore offer a practical alternative for field-based developmental research where participant comfort and compliance are critical. The frontal electrode location (Fp1) captures activity from prefrontal regions involved in executive control and attentional regulation, allowing extraction of frontal spectral indices and event-related potentials (ERP) components. Accordingly, the present study adopts a portable frontal EEG configuration to balance methodological rigor with feasibility in a kindergarten setting.

EEG recordings will be obtained during both resting-state conditions and during an age-appropriate cognitive paradigm designed to assess inhibitory control. Resting-state recordings will be conducted while children sit quietly for approximately one minute with minimal movement. Task-related EEG will be recorded during a simplified Go/No-Go paradigm adapted for preschool children, which has been widely used to assess early inhibitory control and attentional regulation during the preschool years.

To enhance interpretability and avoid exploratory overreach, the trial specifies a limited set of pre-defined neural indices. The primary EEG outcome will be frontal theta power measured during resting state. Frontal theta activity has been associated with functional engagement of prefrontal control systems and demonstrates developmental sensitivity across early childhood (14, 15). A secondary task-related neural index will be the N2 component elicited during the Go/No-Go paradigm. The N2 has been widely interpreted as a neural indicator of conflict monitoring and response inhibition and has been reliably elicited in preschool-aged children using simplified Go/No-Go paradigms (16–18). Because inhibitory control represents a foundational element of executive functioning that is routinely considered within pediatric developmental assessment frameworks, these neural measures are selected as developmentally interpretable functional indicators rather than as direct measures of neural plasticity or structural brain change.

Additional EEG measures will include spectral power indices in the alpha and beta frequency bands to provide complementary information regarding cortical activation patterns. Behavioral performance during the Go/No-Go task, including response accuracy and reaction time, will be analyzed alongside EEG indices to contextualize neural findings. Exploratory analyses will examine associations between changes in gross motor competence and changes in EEG-derived neural indicators. These exploratory analyses are intended to generate hypotheses for future research rather than to establish definitive mechanistic pathways.

EEG data preprocessing will follow standardized procedures for portable EEG recordings. Raw signals will first undergo 50 Hz notch filtering to remove electrical line noise, followed by bandpass filtering between 0.5 and 45 Hz. Data will then be segmented into task-related epochs and corrected using baseline activity from the resting-state recording. Segments contaminated by excessive movement, ocular activity, or muscle artifacts will be identified using amplitude thresholds (e.g., ±80–100 μV) and removed. Remaining trials will be visually inspected by trained analysts to ensure data quality before averaging. Spectral power will be calculated using fast Fourier transform methods, and ERP components such as the N2 will be extracted from averaged task-related waveforms. Preprocessing will be conducted by research staff blinded to group allocation.

Additional measures will be included to provide complementary perspectives on children's everyday functioning beyond structured testing. Parents will complete the Behavior Rating Inventory of Executive Function–Preschool Version (BRIEF-P) (19), which assesses domains including inhibition, shifting, emotional control, working memory, and planning/organization. Teachers will complete the Strengths and Difficulties Questionnaire (SDQ) (20), which evaluates behavioral adjustment, prosocial behavior, hyperactivity, and peer relationships. Questionnaires will be administered at baseline and post-intervention via secure electronic survey. These instruments will serve as supplementary outcomes to provide ecologically valid information regarding children's executive and socio-emotional functioning in daily contexts.

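### The resting-state recording is the wrong baseline for the Go/No-Go epochs: it leaves the N2 without a stimulus-locked zero level

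*Protocol article*

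**What the plan says.** Section 2.6 (Outcomes and data collection procedures) of the protocol article describes two separate EEG conditions. For rest: "Resting-state recordings will be conducted while children sit quietly for approximately one minute with minimal movement". For the task: "Task-related EEG will be recorded during a simplified Go/No-Go paradigm adapted for preschool children". Rest supplies the leading neural endpoint: "The primary EEG outcome will be frontal theta power measured during resting state". The task supplies the next one, which section 2.8 (Statistical analysis) fixes as an amplitude: "A secondary task-related neural index will be the N2 amplitude elicited during the Go/No-Go task". Each has its own mixed model.

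The preprocessing steps run in this order: a 50 Hz notch, "followed by bandpass filtering between 0.5 and 45 Hz", and then "Data will then be segmented into task-related epochs and corrected using baseline activity from the resting-state recording". Artifact segments are next "identified using amplitude thresholds (e.g., ±80–100 μV) and removed", the remaining trials are inspected by eye, and the epochs are averaged. Power comes from a Fourier transform, and "ERP components such as the N2 will be extracted from averaged task-related waveforms".

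The article names no pre-stimulus interval. It also does not say whether the correction subtracts a voltage or normalises power, or to which measures it applies.

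**The concern.** An event-related potential is a voltage measured relative to a reference level tied to its stimulus. A recording made at another time, under another condition, cannot supply that level for a given Go/No-Go trial. If the sentence is followed as written, the epochs are described as corrected although no stimulus-locked zero has been set. Any voltage shift that regularly precedes the stimulus, such as anticipation, would not average out and would be read as part of the N2.

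The same sentence stands ahead of the spectral step, so it can also be read as normalising task power by resting power. Resting activity would then be built into the task index, although the plan treats rest and task measures as distinct indices.

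**Working it through.** The plan gives no figure to reproduce. The check is an algebraic argument, an illustrative simulation and one closed formula.

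**1. What subtracting a resting mean can do.** Let x_i be the N2-window voltage on trial i and c the child's resting mean. The corrected average is mean(x_i − c) = mean(x_i) − c. One constant is removed from every trial, so no trial-specific offset is touched.

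**2. How large c is.** The rest recording lasts about 60 s (section 2.6). Its mean reflects frequencies of roughly 1/60 ≈ 0.017 Hz and below. The high-pass edge is 0.5 Hz, and 0.5 × 60 = 30 times higher. The filter has therefore already removed nearly everything that could make c differ from zero.

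**3. Simulation.** From the protocol: 512 Hz sampling, 50 Hz notch, 0.5–45 Hz band-pass, 60 s of rest. Assumed: 300 children per setting, stationary 1/f^k noise with a raw SD of 20 μV, zero-phase Butterworth filter, about 40 task trials, N2 window 250–400 ms, pre-stimulus window −200 to 0 ms, theta 4–7 Hz. The microvolt values depend on the assumed scale; the ratios and correlations do not.

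| | k = 1.0 | k = 1.5 | k = 2.0 |
|---|---|---|---|
| Signal SD after filtering (μV) | 12.6 | 7.0 | 2.9 |
| SD of resting mean across children (μV) | 0.0383 | 0.0253 | 0.0142 |
| Resting-mean SD / signal SD | 0.0030 | 0.0036 | 0.0049 |
| Trial SD of N2-window mean after resting correction (μV) | 7.07 | 3.95 | 1.45 |
| Correlation of corrected with uncorrected N2 | 0.9995 | 0.9993 | 0.9984 |
| Correlation of corrected N2 with log resting theta | 0.011 | −0.019 | −0.001 |
| SD of averaged N2, resting baseline (μV) | 1.163 | 0.663 | 0.251 |
| SD of averaged N2, pre-stimulus baseline (μV) | 1.729 | 1.013 | 0.390 |
| Ratio of the last two rows | 1.49 | 1.53 | 1.55 |

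Read as voltage subtraction, the correction is inert, and it creates no link between the N2 and resting theta. A 200 ms pre-stimulus baseline made the averaged N2 noisier by a factor of about 1.5. Adding movement-like steps to the noise again gave about 1.5. Systematic pre-stimulus shifts were not simulated.

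**4. If the rule means power normalisation.** Let T and R be log task and log resting power in one band, with equal variances and correlation r. Then corr(T − R, R) = −(1 − r)/√(2(1 − r)) = −√((1 − r)/2).

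| r | 0 | 0.3 | 0.5 | 0.7 | 0.9 |
|---|---|---|---|---|---|
| corr(T − R, R) | −0.71 | −0.59 | −0.50 | −0.39 | −0.22 |

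If resting log power rises by D and task power is unchanged, T − R falls by D. The dependence lies within a band: task alpha or beta would be tied to resting alpha or beta.

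**The case against.** The strongest reply is that a journal article condenses its preprocessing, and that epoch limits and baseline windows belong in a fuller document. That would answer a mere omission. Here a baseline source is stated, and it is unsuitable for the N2, so the point remains.

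A second reply is that slow drift is already handled by the 0.5 Hz high-pass, amplitude rejection and visual inspection, and that the simulation favours leaving the epochs alone on noise grounds. This largely stands. It rules out any promise that a pre-stimulus baseline will sharpen the N2. It does not give the N2 a stimulus-locked zero, nor does it deal with a shift that recurs before each stimulus.

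Third, both arms go through the same blinded preprocessing. No between-arm bias in the N2 has been shown, and none is claimed here.

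A reader might also infer more than the documents support:

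- That the rule ties the N2 to resting theta. A mean voltage is not theta power, and the simulated correlations were between −0.02 and 0.01.
- That resting theta enters a task-theta endpoint with reversed sign. No such endpoint is named: theta is specified at rest only, and alpha and beta are listed without a stated condition.
- That the rule adds noise to the N2. A step that does almost nothing cannot do so.
- That the fixed microvolt rejection threshold is weakened. No figure or derivation supports this.
- That the residual error in each child's N2 can be put in microvolts. That needs the epoch offset SD after filtering and the number of retained trials, and the article gives neither.

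**Conclusion.** The concern holds in a limited form. As a voltage correction for the N2, the stated rule uses a reference that is not time-locked and is near zero after filtering, with an SD of about 0.3–0.5% of the signal SD in simulation. It leaves the N2 without a stimulus-locked zero level. As a power normalisation, it would build resting power into the task index, with a correlation of −0.71 to −0.22 for rest–task correlations of 0 to 0.9. Neither reading is satisfactory, and the text does not say which is meant.

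The first result rests on the stated filter and recording length, plus an assumed noise model and filter type. The second rests on equal variances and on task power being normalised to rest at all. The practical weight is small. The Discussion says that the trial is not powered for firm EEG conclusions and classes these analyses as exploratory, and gross motor competence is untouched. The correction is still worth making, because the N2 is a named endpoint and the change costs almost nothing.

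**What to change.** Replace the sentence in section 2.6 with three statements:

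1. Each Go/No-Go epoch is baseline-corrected to its own pre-stimulus interval (for example −200 to 0 ms) before amplitude rejection and averaging.
2. The resting recording is used only for the resting spectral endpoints.
3. Any task power normalised to rest is reported as a separate exploratory index, with the form of normalisation stated.

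This takes a few sentences and no new data, and can be settled before analysis begins in September 2026 (section 4, Ethics and dissemination). There are two costs. The epochs must include a short pre-stimulus window, and a short baseline can add random noise to the averaged N2 after high-pass filtering. The reason to give for the change is a defined zero level and the separation of rest from task indices, not better precision.
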